**Figure 1 F1:**
[figure not shown]
Design of the cluster study (Emilia-Romagna and Friuli Venezia Giulia): effectiveness of information meetings.

Considering two rounds of information meetings, four topics will be needed (two topics each round) and four interventions will be tested overall. While these are different specific comparisons, the same general hypothesis will be tested: whether information meetings led by pharmacists are effective in changing physicians' behaviour (comparing to no visit on the same topic). The reasons why four comparisons are planned are to better evaluate the feasibility of this kind of intervention (which could be eventually proposed in the Italian NHS on a routine basis) and to have better insight into its effectiveness, since this may depend on the kind of topics and on the extent of information presented.

The first couple of topics chosen (for the spring 2007 round) are: 'drugs for the treatment of benign prostatic hyperplasia', and 'drugs for the primary prevention of osteoporotic fractures in elderly people'. The second couple of topics will be chosen about two-three months before the autumn 2007 round and this choice will depend, as well as for the first two topics, on relevance for clinical practice, limited availability and diffusion of information independent from drug industry, possibility to synthesize clear and evidence-based messages on benefits and risks of therapies and possibility to affect drug prescriptions significantly.

Stratified randomisation will be carried out within each Local Health Authority (LHA), using the number of assisted population per PCG (under or over the mean for that LHA) as stratifying factor. Pharmacists will be randomised along with the PCGs since the meeting scheme (which pharmacist meeting which PCG) will be defined before randomisation: this in order to avoid a 'topic-based' self-selection of visiting pharmacists, which may introduce a bias (doctors receiving intervention A could meet more or less motivated pharmacists, than those receiving intervention B).

About one pharmacist every 8–10 PCGs will get ad hoc training for the study, getting:

• one four-day intensive course (36 hours) on EBM methodology

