### Outcomes

#### Main outcome

difference (%) in NHS prescription of drugs under scrutiny (expressed as DDD per thousand inhabitants/day), comparing those who have/do not have received the specific information. In case of relevant baseline unbalances, statistical adjustment will be sought

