#### Secondary outcomes

• difference in the % of patients who were prescribed the specific drug(s)

• difference in the % of patients who were prescribed the specific drug(s) for the first time (in the previous 12 months)

• difference in expenditure for the specific drug (per 1000 patients/day)

• difference in NHS prescription of drugs under scrutiny (expressed as DDD per thousand inhabitants/day), comparing those who have received the "traditional" vs "enriched" format, and any information vs no information (Sardinia study only)

• differences in the main and secondary outcomes in each of the regions involved (cluster study only);

• differences in the main and secondary outcomes according to the n. of assisted population in the related PCG (cluster study only)

• differences in the main and secondary outcomes according to the terziles of physicians age

• adjusted difference in prescribed DDD per 1000 patients/day according to a statistical model, considering as possible covariates: overall prescription in DDD per 1000 patients day at baseline; n. of physicians in the specific PCGs; n. of assisted population; region (Emilia-Romagna or Friuli Venezia Giulia); geographical location (mountain, hill, plain, urban centre – according to definitions given by the Italian Statistics Institute); age distribution of assisted population (in quartiles); % females in the assisted population; physician age; total physician drug expenditure (excluding drugs under scrutiny); % assisted population with polyprescription (≥ three drugs of different classes); n. new prescriptions (in the last 12 months); month of evaluation; participation to the information meetings; % exact answers to the questionnaire testing knowledge (see additional file 1);

• difference in the variability (expressed as standard deviations) of prescription of drugs under scrutiny within PCGs (cluster study only)

• difference in knowledge (measured through the n. of correct answers to a specific anonymous questionnaire, see additional file)

• difference in attitudes (measured through the answers to a specific questionnaire, see additional file)

Drugs whose NHS prescription will be considered for the first two topic chosen are specified here below:

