### Statistical analysis

The statistical analysis will be performed according to the intention-to-treat principle, analysing physicians' prescriptions according to the treatment group to which they were randomly allocated (as single GPs or as members of PCGs), and independently from their participation to the outreach visits. A 'modified intention to treat' will be considered in case some physician should not be actually offered the randomised intervention (for example, if pharmacists should become unavailable in a given area for organisational reasons or if health policy issues should arise, e.g. lack of agreement with medical syndicates, etc). Secondly, a by treatment analysis will also be performed considering only physicians who actually participated to the visits.

T-test (for continuing variables), chi-square test (for discrete variables) and multiple linear regression will be used, the latter to investigate how specific variables (like baseline prescriptions, region, size of PCG, size of assisted population, age and sex of GP, month of follow-up, etc) can affect outcomes. Analysis of covariance (ANCOVA) will be used for evaluating primary outcomes in case relevant baseline imbalances (for example in the prescription of targeted drugs) will make statistical adjustment necessary.

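### Baseline adjustment of the primary outcome depends on an undefined imbalance, so the primary estimator is not fixed in advance and the precision in baseline prescribing is usually lost

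*Protocol article*

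**What the plan says.** The main outcome is the "difference (%) in NHS prescription of drugs under scrutiny (expressed as DDD per thousand inhabitants/day), comparing those who have/do not have received the specific information". The same section adds: "In case of relevant baseline unbalances, statistical adjustment will be sought".

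The Statistical analysis section gives the tools: "T-test (for continuing variables), chi-square test (for discrete variables) and multiple linear regression will be used". The regression has an explanatory purpose: "the latter to investigate how specific variables (like baseline prescriptions, region, size of PCG, size of assisted population, age and sex of GP", with month of follow-up and an open end to the list. On the primary outcome it says that "Analysis of covariance (ANCOVA) will be used for evaluating primary outcomes in case relevant baseline imbalances" make adjustment necessary, with prescribing of the targeted drugs as an example.

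Under Secondary outcomes there is a separate "adjusted difference in prescribed DDD per 1000 patients/day according to a statistical model, considering as possible covariates". The list begins with "overall prescription in DDD per 1000 patients day at baseline; n. of physicians in the specific PCGs; n. of assisted population; region". It later includes attendance at the meetings and the share of correct answers to the knowledge questionnaire.

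For the cluster trial, the Intervention/Exposure section says: "Stratified randomisation will be carried out within each Local Health Authority (LHA), using the number of assisted population per PCG", split at the LHA mean. No stratification is described for Sardinia.

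**The concern.** Two analyses of the primary outcome are possible, an unadjusted t-test and an ANCOVA. The choice between them rests on a word that has no threshold, no decision-maker and no fixed covariate set. This is a rule that the article itself states, in two places, so it is not a detail left to a fuller document.

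Two things are at stake. First, the primary result is not tied to one estimator before the data are seen. Second, baseline prescribing carries information on follow-up prescribing, and a rule that uses it only after a chance imbalance will usually discard it. That matters where the expected number of PCGs only just meets the stated need. In the cluster trial, prescribing differences between LHAs also stay in the error term, although randomisation was balanced within LHA.

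**Working it through.** **Inputs from the article.** Table 2: finasteride plus dutasteride, ICC 0.08, 154 PCGs for a 10% difference, two-tailed, 15 GPs per PCG. Expected recruitment: about 150 PCGs. This drug pair is a main indicator for the first prostate topic.

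**Assumed.** Two-sided alpha 0.05 and 80% power (neither is stated); the correlation r between baseline and follow-up PCG-level prescribing; the share of PCG variance lying between strata; and a t-test applied to PCG means, so that clustering is respected.

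**Step 1: the plan's own figure.** The SD is not given, so 154 cannot be reproduced independently. The design effect is 1 + 14 × 0.08 = 2.12. Back-solving, CV = √(154 × 15 / 2.12 / 4) × 0.10 / (1.960 + 0.842) ≈ 0.59. One internal check works: bisphosphonates need 238 PCGs at 10%, and 238 / 1.5² = 105.8, which matches the stated 106 at 15%.

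**Step 2: gain from always adjusting.** ANCOVA multiplies the variance by (1 − r²), so the number needed is 154 × (1 − r²), rounded up. Power with 150 PCGs is Φ(√(150 / [154(1 − r²)]) × 2.802 − 1.960).

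| r | PCGs needed | Power with 150 PCGs |
|---|---|---|
| unadjusted | 154 | 79% |
| 0.3 | 141 | 83% |
| 0.5 | 116 | 89% |
| 0.7 | 79 | 97% |
| 0.8 | 56 | over 99% |

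If 154 had been sized for 90% power, the powers would be 89% unadjusted and 92%, 96% and 99% at r = 0.3, 0.5 and 0.7.

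**Step 3: what the conditional rule delivers.** Here relevant is assumed to mean a baseline difference at p<0.05. Simulation used 150 PCGs and 10,000 runs per setting.

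| r | Power, rule | Power, always ANCOVA | Type I, rule | Type I, whichever test is significant |
|---|---|---|---|---|
| 0.5 | 79% | 89% | 4.4% | 7.3% |
| 0.7 | 80% | 97% | 3.7% | 8.4% |
| 0.9 | 81% | about 100% | 2.4% | 9.4% |

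The trigger fires in about 5% of trials, as it must under randomisation. Power therefore stays close to the 78–79% of the t-test alone.

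**Step 4: strata left out.** Simulation used 160 PCGs in 20 strata (an assumed layout) with 10,000 runs per setting.

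| Variance between strata | Type I, strata omitted | Power, strata omitted | Power, strata modelled |
|---|---|---|---|
| 10% | 4.0% | 82% | 85% |
| 30% | 2.1% | 85% | 92% |
| 50% | 0.9% | 89% | 98% |

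The mismatch between standard error and randomisation is in the conservative direction.

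**The case against.** The strongest reply is that adjustment is already planned. The secondary adjusted outcome lists baseline prescribing with no imbalance condition, and assisted population and region appear there and in the explanatory regression. Stratum terms are also often left to a full analysis plan. Part of this stands: adjustment is not absent from the plan, and silence on LHA alone would be a weak point. But the secondary model does not fix the primary estimator. Its covariates are only possible ones, its baseline item is overall prescribing rather than clearly the target drug, and two covariates (attendance and questionnaire score) arise after randomisation and may be affected by the intervention.

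A reader might also infer more than the article supports:

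- **That the rule inflates the false-positive rate.** As written, the trigger is a baseline imbalance, not the outcome. Applied mechanically, it is conservative, and so is omitting strata. The 7–9% figures need an analyst who picks the significant result, which the article does not propose.
- **That most of the precision is thrown away.** The variance reduction is r², which exceeds one half only above r ≈ 0.71. At r = 0.3 it is 9%.
- **That the trial is clearly short for alendronate and risedronate.** The 218 and 374 PCGs in Table 2 are for 10%, while the sample size text gives 15% for bisphosphonates. At 15% they become 218 / 2.25 ≈ 97 and 374 / 2.25 ≈ 166. Alendronate is then within 150 and risedronate is near it. Only the class row is marked 15%, so the single-drug target is arguable.
- **That a matching saving can be stated for Sardinia.** The article gives no required number there, the roughly 900 GPs are spread over three arms, and the GP-level correlation need not equal the PCG-level one.

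**Conclusion.** The point holds in limited form. The primary outcome has a stated but undefined adjustment trigger, so the estimator is not fixed in advance, and under a p<0.05 reading about 95% of trials would use the unadjusted test. The cost is mainly power. For finasteride plus dutasteride it is the gap between 79% and 83–97% at r = 0.3–0.7 with 150 PCGs, which is small at the low end and substantial at the high end. These sizes rest on an assumed r, an assumed alpha and power, and a t-test that respects clustering. Type I error is at or below nominal unless the choice is made with outcomes in view; the undefined trigger leaves that open. In the cluster trial, LHA is in no listed analysis and assisted population only in secondary or explanatory models, which is a further loss of power of unknown size. This is a near-costless improvement, not a flaw that invalidates either trial.

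**What to change.** In both trials, make the primary analysis an ANCOVA on six-month DDD per 1000 per day. Adjust for pre-round DDD of the same target drug over a period fixed beforehand, whatever imbalance is observed. In the cluster trial, also adjust for LHA and the above/below-mean population stratum, and analyse PCG-level data or include a PCG random effect. Keep covariates that arise after randomisation, such as attendance and questionnaire score, out of any model that estimates the treatment effect. Report the unadjusted difference as supportive, and delete the conditional wording in both the Main outcome and Statistical analysis sections.

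The cost is wording and some degrees of freedom. Monthly prescription data are already to be retrieved, and the present rule itself presupposes baseline values. With 150 PCGs and, for illustration, 20 strata, the model has 22 parameters (20 for strata, one for arm, one for baseline) and leaves 128 residual degrees of freedom in a PCG-level analysis.

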### Organizational characteristics

CeVEAS will coordinate and monitor all the aspects of the study and will be in close connection with the Health Authorities in charge of the local organization. CeVEAS will also provide the necessary training to the pharmacists involved, and will carry out the final evaluation of the study. Regional Health Authorities of Emilia-Romagna, Friuli Venezia Giulia and Sardinia will help select the Local Health Authorities where the study will be carried out, and will participate to the local organization of the project. Local Health Authorities (LHAs) will ensure the local organization, selecting "outreach" pharmacists, promoting their training, and promoting and scheduling the outreach visits. LHAs will also ensure the retrieval of drug prescribing data for the entire study period. Regional and Local Health Authorities do not need previous experience in setting outreach visits programs, the only requirement being the availability of reliable drug prescription databases for retrieval of GPs' prescribing data.

### Steering Committee

A Steering Committee (SC) was nominated in September 2006 to approve the final version of the protocol and to address ethical matters. Specifically, the SC will supervise study organisation, conduct and analysis of results, and will be made of 16 components: a chairman; three representatives of the coordinating centre; one representative of the Regional Health Authority, two representatives of GPs and one representative of pharmacists for each of the three participating regions. Specifically the SC will:

• verify that all the Health Authorities involved adhere to the minimum requirements indicated in the study protocol, in keeping with the pragmatic nature of the study

• verify that data have been adequately checked for quality

• supervise the production of reports to inform the participating Health Authorities about the progression of the study

• monitor the scientific literature to seek for possibile new relevant information on the discussed topics

• evaluate possible amendments to the protocol

## Discussion

The two proposed RCTs will let us better understand the potential usefulness of NHS pharmacists assuming a more active role in transferring evidence-based information to physicians. Besides data on prescribing impact, the studies will provide qualitative insight on the feasibility of such information programs, with special attention to how different organizational settings in different regional areas may lead to better or worse implementation. As already said, these studies represent an unprecedented effort to accomplish such evaluations on quite a large scale and in a 'natural' organizational setting, which would be minimally altered by the interventions themselves. Moreover, the two RCTs will test two different strategies of information delivery: using small groups or one to one meetings. While these strategies will not be directly compared (being not employed in the same study but in two different ones), their feasibility and impact will be critically evaluated, also in light of other experiences described in the scientific literature and of methods used by the pharmaceutical industry to bring information to doctors on a large scale.

Last but not the least, the role of the format of medical information will be investigated: this could be a critical part in the implementation of information programs and its importance may be often underestimated, considering that medical schools generally do not offer the necessary tools to unscramble data published in the scientific literature; that average doctors do not have enough time to select and read what may add relevant information to their knowledge; and that, eventually, the uptake of this information may be facilitated by offering it in a clear, direct and appealing fashion, looking at the context of clinical practice [17].

As usually happens, the evaluation of complex interventions is intricate given the many different variables into play: it is the other side of the pragmatic nature of these RCTs, which is also, and undoubtedly, one of their strengths. Moreover, the ambitious quantitative hypothesis to be tested (10 or 15% difference in doctors' prescriptions) will not be easily demonstrated, in spite of the involvement of about 2000 physicians in the cluster RCT and about 900 in the single doctors RCT: an even larger sample size would have been necessary to see smaller but still relevant prescribing differences.

### Feasibility

The Centre for the Evaluation of the Effectiveness of Health Care (CeVEAS), a NHS Centre dedicated to the production and implementation of independent information, has already been implementing outreach visit programs in selected areas of Emilia-Romagna starting from 2001, using "Information Packages on Drugs" ^® ^(drug information bulletins, registered in the International Society of Drug Bulletins since 2006, developed to facilitate knowledge transfer). However, the large scale feasibility of such information program has not been formally tested, neither a formal impact assessment on physicians' knowledge, attitudes and prescribing practice has been carried out.

### Ethical aspects

Between November 2006 and March 2007, the protocol was sent to the Local Ethics Committees (LEC) of the Health Authorities involved. Most of the LEC have already approved the protocol, some specifying that it was unnecessary to analyse it formally since no ethical problems arise in carrying out a randomisation differentiating the kind of information actively discussed during the outreach visits. In any case, the same information will be available to everybody outside the study meetings. At the end of each follow-up period, the information discussed during outreach visits will be proactively sent to each physician unexposed to that specific information during the outreach visits.

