**Methods/Design:**

Two RCTs are planned:

1) a two-arm cluster RCT, carried out in Emilia-Romagna and Friuli Venezia Giulia, will evaluate the effectiveness of small group meetings, randomising about 150 Primary Care Groups (corresponding to about 2000 GPs) to pharmacist outreach visits on two different topics. Physicians' prescriptions (expressed as DDD per 1000 inhabitants/day), knowledge and attitudes (evaluated through the answers to a specific questionnaire) will be compared for target drugs in the two groups (receiving/not receiving each topic).

2) A three-arm RCT, carried out in Sardinia, will evaluate both the effectiveness of one-to-one meetings (one pharmacist visiting one physician per time) and of a 'new' information format (compared to information already available) on changing physicians' prescription of specific drugs. About 900 single GPs will be randomised into three groups: physicians receiving a visit supported by "traditional" information material, those receiving a visit with "new" information material on the same topic and those not receiving any visit/material.

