### Intervention/Exposure

#### Emilia-Romagna and Friuli Venezia Giulia study (cluster RCT)

A cluster RCT will be performed. PCGs will participate to two rounds of small group information meetings where a trained pharmacist, possibly supported by a GP (a "referent", delegate by the PCG), will provide information, discussing the contents of a bulletin specifically developed about the main studies/literature available on benefits and risks of drugs for preventing and/or curing a specific disease (enriched format) [17].

Within each round of visits (taking place in spring and autumn of 2007, respectively), PCGs will be randomised in two groups: those receiving information about a specific topic and those not receiving it (Fig. 1). To improve acceptability to Local Health Authorities and sample efficiency, PCGs not receiving information about one specific topic (e.g. topic A) will receive another topic (e.g. topic B). Two evaluations will then be carried out: for topic A related outcomes, recipients vs non recipients of topic A will be compared; conversely, for topic B related outcomes, the comparison will be between recipients vs non recipients of topic B.

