### Follow-up

The follow-up time will be six months after each intervention. A further evaluation will be carried out after 12 months to assess persistence

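### On the plain reading, controls are mailed the withheld topic about six months before the 12-month persistence evaluation, which then no longer compares visited GPs with GPs left without the material

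*Protocol article*

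**What the plan says.** The Follow-up section of the protocol article consists of two sentences: "The follow-up time will be six months after each intervention. A further evaluation will be carried out after 12 months to assess persistence". The term follow-up is attached to six months, and the 12-month look is named separately.

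The Ethical aspects section commits the trial to an active mailing: "At the end of each follow-up period, the information discussed during outreach visits will be proactively sent to each physician unexposed" to the topic in question. It gives no month. It also notes that anyone can obtain the same content outside the meetings.

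Three statements define what the controls are meant to be:

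- The main outcome is a prescribing difference "comparing those who have/do not have received the specific information".
- In the cluster trial, the general hypothesis is the effect of meetings, "comparing to no visit on the same topic" (Intervention/Exposure, text after Figure 1). Groups that do not get one topic get the other, so each arm is the control for the other arm's topic.
- In Sardinia, the Abstract describes the control arm as "those not receiving any visit/material".

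No section holds the mailing back until the 12-month evaluation is complete, and none says how the 12-month analysis would allow for it.

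**The concern.** A persistence evaluation asks whether the gap seen at six months is still there at 12. That needs a control group whose condition stays the same between the two looks. If every control is sent the material in between, a narrowing gap has two explanations: the effect faded in visited GPs, or the controls moved towards them. The randomised comparison cannot tell these apart.

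If the mailing changes prescribing at all in the intended direction, the error runs one way, towards a conclusion that the effect does not last. A health service deciding whether to make such visits routine, or how often to repeat them, would use exactly that result.

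**Working it through.** **Inputs from the protocol article**

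- Length of follow-up: six months (Follow-up).
- Persistence evaluation: 12 months (Follow-up).
- Mailing to controls: end of each follow-up period (Ethical aspects).
- Target difference: 10%, or 15% for bisphosphonates (Sample size estimates).
- Effect of written information alone: no figure given. The Background says that simple diffusion does not appear to change prescribing.

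**Timeline**

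| Month | Visited GPs | Control GPs for that topic |
|---|---|---|
| 0 | visit and material | nothing on this topic |
| 6 | main comparison | main comparison, then material mailed |
| 12 | persistence evaluation | persistence evaluation, with the material held for 12 − 6 = 6 months |

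If the 12 months were counted from the end of follow-up, the evaluation would fall at month 18 and controls would have held the material for 18 − 6 = 12 months.

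**Which comparisons are touched**

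- *Cluster trial:* both topic comparisons in each round, because each arm is the other's control.
- *Sardinia:* the comparison of visits with no visit or material.
- *Traditional versus enriched format in Sardinia:* not clearly affected, since both arms already received the topic.
- *Month 6:* not affected, because the mailing follows it.

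**Size, under an assumption**

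Let d be the visit effect, p the share of it that persists at month 12, and f the mailing's effect in controls as a fraction of d. The observed 12-month difference is then

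d × (p − f).

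With full persistence (p = 1) this is d × (1 − f):

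| f (assumed) | d = 10% | d = 15% |
|---|---|---|
| 0 | 10% | 15% |
| 0.25 | 7.5% | 11.25% |
| 0.5 | 5% | 7.5% |

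The difficulty is one of identification. With d = 10%, an observed 5% fits p = 1 with f = 0.5, p = 0.75 with f = 0.25, or p = 0.5 with f = 0. The data give p − f, not p.

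Adjustment does not solve this. The Statistical analysis section lists month of follow-up as a possible covariate, but the plan mails every control, so no randomised group remains without the material. The monthly data could show whether control prescribing shifts after the mailing, but that would be a before-after reading, open to secular trends.

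No power figure is given here, because the article states no power for any comparison.

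**The case against.** **The timing is inferred.** The Ethical aspects section names no month, and the section headed Follow-up covers both the six-month and the 12-month looks. If each follow-up period is meant to run to the last look of each round, the conflict disappears. That reading is possible. But the only duration the article gives to follow-up is six months, and it calls the 12-month look a further evaluation. The six-month reading is the more literal one, and nothing excludes it.

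**Controls stay unvisited.** A reader might infer that the trial has no valid control group at 12 months. The documents do not support that. The cluster trial's hypothesis is about visits, controls still have had none on that topic, and the content was obtainable by anyone throughout. What changes is that passive availability becomes an active mailing. A visit contrast survives, but against a different comparator.

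**Mailing may do almost nothing.** The trial's own premise in the Background is that diffusion alone does not seem to alter prescribing, which puts f near 0. This stands as a limit on size. It does not make zero safe to assume: the trial also tests whether the format of written material matters. That question concerns material used with visits, so it does not fix f either.

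**It is a follow-on evaluation, and the mailing is an ethical commitment.** Both are true. The 12-month look is not listed separately among the outcomes, and most local ethics committees had already approved the protocol. This limits the weight of the point and adds a little to the cost of changing it.

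**Conclusion.** The point holds in a limited form. Followed as written, the two sections place an active mailing to all controls about six months before the persistence evaluation. The 12-month result would then measure visit versus later mailed information, and any catch-up by controls would be read as lost persistence.

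The size cannot be computed from the article. Over an assumed range of f from 0 to 0.5, a fully persistent 10% difference would appear as anything from 10% down to 5%, with the article's own premise favouring the upper end. The direction, towards no persistence, assumes that the mailing moves prescribing the same way as the visit.

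A reader might go further and conclude that the main results are contaminated or that a stated power is lost. Neither follows: the six-month comparison comes before the mailing, and no power is stated. The change is still worth making, because it is cheap and because analysis cannot recover the comparison once the mailing has gone out.

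**What to change.** State in both Follow-up and Ethical aspects that unexposed GPs are sent a round's material only after that round's 12-month prescribing window has closed. If this was always the intention, one clause in each section is enough.

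The cost is an active mailing about six months later and a small amendment for the Steering Committee to consider, possibly with notice to the ethics committees. The content remains obtainable by everyone in the meantime, as the article already says.

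If the month-6 mailing has to stay, report the 12-month contrast as *visit versus later mailed information*, give the mailing date beside the result, and do not present it as persistence against an unexposed control. That costs only wording, but it gives up the randomised answer on persistence against controls who were not sent the material.
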